#### Data storage and security

All trial data will be securely stored in a dedicated EDC system. This system employs robust security measures, including encryption and access controls, to ensure the confidentiality and integrity of the data. Trial data will be retained for a minimum of 10 years after the completion of the study in accordance with regulatory requirements and sponsor policies. This retention period allows for the preservation of data for potential future analyses, audits, or regulatory inspections. Measures will be implemented to safeguard the confidentiality and privacy of participant data, including de-identification of personal identifiers and compliance with applicable data protection laws and regulations.

#### Data analysis plan

The intention-to-treat (ITT) population will include all patients who are randomized while exclude those who withdrew consent; modified ITT (mITT) population will exclude those whose CTA are not interpreted by the study radiologists, and those with the corresponding AI process failing, and those who withdrew consent; while the Per-protocol (PP) population will only include patients who receive the randomized treatment and do not exhibit major protocol violations, excluding (1) those who withdrew consent; (2) those whose CTA are not interpreted by the study radiologists; (3) those with the corresponding AI process failing; (4) those with the participating radiologists chose not to review AI suggestions, which will be recorded by the background record.

The hypothesis of the study is that the patient-level sensitivity in the intervention arm is superior to that in the control arm, and the patient-level specificity is noninferiority, with a noninferiority margin of 5%. A comparison between the experimental group and the control group for the two primary outcomes will be conducted using the chi-square test or Fisher’s exact test. The results will include the *p* value (2-sided) and the ratio of patient-level sensitivity and specificity. The primary analysis will be based on the ITT population.

Continuous variables will be reported as the means with standard deviations (SDs) or medians with interquartile ranges (IQRs), depending on their distributions. Categorical variables will be presented as numbers and percentages. Statistical significance was set at *p* < 0.05. A 95% CI will be calculated using the Clopper-Pearson method.

The following subgroups will be included:Centers (25 centers), provinces (10 provinces), geographical areas and physician working experiences (working experiences of < 10 years vs. ≥ 10 years) and physician level (junior radiologists vs senior radiologists).Size (< 5 mm vs. ≥ 5 mm) and locations of intracranial aneurysms (anterior vs posterior, internal carotid artery vs. middle cerebral artery vs. anterior cerebral artery vs. posterior communication artery vs. anterior communication artery vs. vertebral basilar artery vs. others).Gender of patients (male vs. female), age (≤ 54 years or. > 54 years), SAH status (with vs. without SAH).History of head DSA or surgery (yes vs. no).Subsequent head DSA or surgery (yes vs. no).

In this study, only participants who have underwent head CTA will be randomized and included in the analysis. Therefore, missing CTA exams are not expected in the trial. The potential missing data include the following: (1) study reports lost: patients whose CTA exams were accidentally interpreted by other radiologists not involved in the trial, or the reports cannot be retrieved due to other reasons. (2) Baseline characteristic information: the missed data will be marked with “NA” and will not be included in the analysis.

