**Fig. 2 Fig2:**
[figure not shown]
Procedures of patient enrollment and randomization. AI = artificial intelligence, CTA = CT angiography, mRS = Modified Rankin Scale

The AI-processed image series provided suggestions for suspected intracranial aneurysms, and the radiologists could accept or reject the suggestions according to their own judgment. Both True-AI and Sham-AI can be displayed in an identical human-AI interaction platform.

Each center includes at least two participating radiologists, junior radiologists (usually attending radiologists) writing the initial report, and senior radiologists reviewing and releasing the report, which is the standard of care in China and the radiology community [25]. The participating radiologists need to meet the predefined requirements and been trained for diagnosis of intracranial aneurysms. They will assess the quality of images and data availability. In both study groups, the junior radiologists will interpret CTA images firstly without AI assistance; if aneurysms are diagnosed by junior radiologist, he/she is required to input the three-dimensional coordination of each diagnosed aneurysm in the study website.

Then the AI system act as a second reader, and will judge whether the radiologist’s diagnosis is overlapped with the AI suggestions according to the three-dimensional coordination, and only present AI suggestions that are not overlapped with radiologist’s diagnosis on the study website (the radiologist will not have access to the original AI predictions except for the presenting results). The junior radiologist will continue to independently re-assess the additional suggestions, and potentially modify his/her initial judgment accordingly, to determine his/her final report (Fig. 3). The senior radiologist has access to the first reader’s assessment and will review and release the official radiological report. They can assign cases to a consensus meeting when the radiologists find a case difficult or equivocal, where the case will be discussed at their local site for a final decision. After the diagnosis is made, the patients will be treated according to national and institutional guidelines. The requirements for participation, adherence, and protocol deviations and study monitoring are provided in the Supplementary Appendix.

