**Fig. 3 Fig3:**
[figure not shown]
Schematic diagram showing how AI suggestions will be presented according to the diagnosis of junior radiologists. The workstation will judge whether there is overlap between AI suggestions and the initial diagnosis of the junior radiologists; if the two results are identical (same), no additional aneurysms will be presented on the study website; if there are no overlapped with AI suggestions (different), the additional aneurysms will be presented in the workstation. ^#^The study website will only present additional aneurysms by AI models, and they would be true-positive aneurysms or false-positive aneurysms

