#### Description of the investigational product

The investigational product is a deep-learning-based intracranial aneurysm detection model: True-AI model and Sham-AI model. For both models, the full-resolution Digital Imaging and Communications in Medicine (DICOM) images are directly input without any preprocessing or rescaling. The images will be displayed in a separate web-based platform (Fig. S1 in the Supplementary Appendix).

True-AI model was developed in 16,422 CTA examinations and had a patient-level sensitivity, lesion-level sensitivity and specificity of 0.93, 0.87, and 0.79 in an independent validation dataset of 1810 cases, respectively. The Sham-AI model was developed in the same dataset with a different strategy. It was designed to have a sensitivity close to zero and a similar specificity to True-AI, so that it would not help radiologists detect additional aneurysms and expose the radiologists to the same incidental effects of the Standard-AI at the same time. Finally, Sham-AI had a patient-level sensitivity, lesion-level sensitivity, and specificity of 0.02, 0.01, and 0.80, respectively, in the same validation dataset ([name], [name], [name], [name], [name], [name], [name], [name], [name], [name], et al: Propose and validation of a placebo control for AI models in intracranial aneurysms detection: a Multi-centre, Multi-reader, Blinded Crossover Study, unpublished). We also have evaluated the influence of Sham-AI on radiologists’ diagnosis of intracranial aneurysms in a crossover, blinded diagnostic study in 28 radiologists from 7 geographically different hospitals across China, and find that radiologists had noninferior sensitivity and specificity with the aid of Sham-AI to that of reader-alone (noninferiority margin of 5%) ([name], [name], [name], [name], [name], [name], [name], [name], [name], [name], et al: Propose and validation of a placebo control for AI models in intracranial aneurysms detection: a Multi-centre, Multi-reader, Blinded Crossover Study, unpublished). The architecture of the True-AI and Sham-AI models is shown in Fig. S2 in the Supplementary Appendix.

A dedicated medical workstation (DeepWise Aneurysm Aided Detection Software, v1.0.0.2) is designed to demonstrate the DICOM images. The workstation will only present three-dimensional coordination for unoverlapped aneurysms on the study website.

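### Dropping cases with unreviewed AI suggestions from the per-protocol set selects on missed aneurysms in the True-AI arm only, so per-protocol sensitivity leans modestly toward True-AI; the ITT coprimary tests are unaffected

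*Protocol article*

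**What the plan says.** The Data analysis plan defines three populations. The per-protocol set drops patients who withdrew consent, those not read by study radiologists, those with a failed AI process and, as criterion (4), "those with the participating radiologists chose not to review AI suggestions, which will be recorded by the background record". The first three exclusions also define the mITT set, so criterion (4) is the only listed exclusion that separates the two. The same section states: "The primary analysis will be based on the ITT population". The article gives the per-protocol set no explicit role.

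Under Interventions, Procedures, the junior radiologist reads first without AI. The system will then "only present AI suggestions that are not overlapped with radiologist’s diagnosis on the study website". The legend to Fig. 3 adds that "if the two results are identical (same), no additional aneurysms will be presented on the study website", and that what is shown may be right or wrong: "The study website will only present additional aneurysms by AI models, and they would be true-positive aneurysms or false-positive aneurysms".

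Description of the investigational product reports that True-AI "had a patient-level sensitivity, lesion-level sensitivity and specificity of 0.93, 0.87, and 0.79 in an independent validation dataset of 1810 cases", and that "Sham-AI had a patient-level sensitivity, lesion-level sensitivity, and specificity of 0.02, 0.01, and 0.80, respectively".

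**The concern.** Criterion (4) is an adherence rule, but adherence can be observed only where there is something to review. Whether a suggestion is pending depends on two things that arise after randomisation: the algorithm in the arm and the result of the junior's first read.

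In a True-AI patient with an aneurysm, a pending suggestion often means the junior missed it. If nobody looks at the suggestion, the patient is likely to end as a false negative, and the rule removes that false negative from the denominator. In the Sham-AI arm, pending suggestions are almost all false and nearly unrelated to whether the aneurysm was missed, so the rule removes found and missed patients almost in proportion.

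At stake is a supportive analysis. Its sensitivity contrast would no longer compare randomised groups and would lean toward True-AI, even if the AI altered no reader's decision.

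**Working it through.** **The plan's own figure.** Inputs from Sample size calculation: 0.65 and 0.75, one-sided α 0.025, power 0.80, 5% attrition. n per arm = [1.960·√(2·0.70·0.30) + 0.842·√(0.65·0.35 + 0.75·0.25)]² / 0.10² = 328.5, so 329. Then 329/0.95 gives 347 per arm, or 694. This matches the article, and the same planning sensitivities are used below.

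**Inputs for the check**, among reference-positive patients:
- Found at first read: 0.65; missed: 0.35. Assumption: the planned Sham-AI arm value stands in for the first read.
- c, the share of those misses that True-AI flags: 0.93 (stand-alone figure) down to 0.50 (pessimistic assumption). If all 7% of patients that True-AI fails to flag were also first-read misses, c would be (0.35 − 0.07)/0.35 = 0.80. Values below 0.80 therefore imply worse performance in use than in validation.
- Displayed false prompt: 0.21 (True-AI) and 0.20 (Sham-AI), taken as 1 − specificity.
- s, the share of prompted cases not reviewed: not in the article; 2% to 20% assumed, unrelated to the type of prompt.
- Unreviewed misses stay missed.

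**Step 1: who carries a prompt and so can be dropped.**
- True-AI, c = 0.93: missed 0.35·(0.93 + 0.07·0.21) = 0.331; found 0.65·0.21 = 0.137. Share missed = 0.331/0.467 = 71%. With c = 0.50 it is 0.212/0.348 = 61%.
- Sham-AI: missed 0.35·(0.02 + 0.98·0.20) = 0.076; found 0.65·0.20 = 0.130. Share missed = 0.076/0.206 = 37%, against 35% overall.

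**Step 2: per-protocol sensitivity in True-AI**, taking 0.75 as the ITT value:

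PP = (0.75 − 0.65·0.21·s) / (1 − 0.35·[c + (1 − c)·0.21]·s − 0.65·0.21·s)

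The proper comparator is the sensitivity with every suggestion reviewed, 0.65 + 0.10/(1 − s), because ITT is itself diluted by non-review.

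At s = 10%, c = 0.93: 0.73635/0.95329 = 0.772. At c = 0.50: 0.73635/0.96518 = 0.763. Full review: 0.65 + 0.10/0.90 = 0.761. Sham-AI stays at about 0.65.

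| s | Full review | PP, c = 0.50 | PP, c = 0.93 | Excess over full review (points) |
|---|---|---|---|---|
| 2% | 0.752 | 0.753 | 0.754 | about 0 to 0.2 |
| 5% | 0.755 | 0.756 | 0.761 | 0.1 to 0.6 |
| 10% | 0.761 | 0.763 | 0.772 | 0.2 to 1.1 |
| 20% | 0.775 | 0.777 | 0.797 | 0.2 to 2.2 |

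**Step 3: second calibration.** Take 0.75 as the full-review value instead, and give Sham-AI its 0.02 sensitivity. With c = 0.93 the full-review difference is 0.098. The per-protocol differences are 0.100, 0.104, 0.110 and 0.123 at s = 2%, 5%, 10% and 20%, an excess of 0.2, 0.6, 1.2 and 2.5 points. Sham-AI per-protocol sensitivity stays at 0.652–0.653.

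**Step 4: no AI effect.** Put 0.65 in place of 0.75 in Step 2. At s = 10%, True-AI per-protocol sensitivity is 0.63635/0.96518 = 0.659 (c = 0.50) to 0.63635/0.95329 = 0.668 (c = 0.93). Against Sham-AI at 0.650 this is a spurious difference of about 0.9 to 1.7 points. Leaving out misses that carry only a false prompt, the (1 − c)·0.21 term, lowers the bottom to 0.7.

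**Step 5: when the direction holds.** Dropping prompted cases raises the result only if they would have had a lower sensitivity than the rest of the arm. In the Step 2 model that requires c above about 0.39 to 0.46 for s from 2% to 20%. The 0.80 implied by the article's figures is well clear of this.

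**The case against.** The strongest case on the other side has five parts.

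1. **Comparator.** A per-protocol analysis is meant to show the effect when suggestions are reviewed, so a gap from ITT is partly legitimate. This stands. A reader might infer that the whole rise from 0.750 to about 0.763–0.772 at 10% non-review is bias. It is not: full review alone would give 0.761, and at c = 0.50 almost all of the rise is recovery of that effect.

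2. **Unknown driver.** The article gives no non-review rate, and adherence and monitoring are placed in a Supplementary Appendix that is not shown. This stands; at low rates the excess is negligible.

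3. **Another reading of criterion (4).** If it covers readers who skip the AI step before any output appears, whatever that output would have been, exclusion is balanced by arm and the bias vanishes. The wording does not say so, and choosing not to review suggestions presupposes that there are some. It does show how the rule can be repaired.

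4. **Senior review.** The endpoint comes from released reports, after a senior radiologist has seen the same display. Some unreviewed misses will be caught, and a patient with several aneurysms may already count as a true positive. This weakens the link, so the figures above are toward the upper side. Removal is enriched for misses, not confined to them.

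5. **Role.** A reader might infer that the superiority claim itself is compromised, or that a per-protocol result will be offered as confirmation of it. The article supports neither: the coprimary tests are on ITT, and per-protocol has no stated role.

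**Conclusion.** The point holds, at modest size. As written, and on its natural reading, criterion (4) selects on first-read misses in True-AI (about 61–71% of those open to exclusion, against 35% overall) and hardly at all in Sham-AI (37%). The per-protocol sensitivity contrast therefore leans toward True-AI.

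Against full review, the excess is about 0.2–1.1 points at 10% non-review (1.2 under the second calibration), up to about 2–2.5 points at 20%, and about 0.2–0.6 points or less at 2–5%. With no AI effect, the rule alone produces +0.7 to +1.7 points at 10%.

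The size rests on the assumed non-review rate, on validation performance carrying over, on unreviewed misses mostly staying missed, and on exclusion applying only where something was displayed. The primary analysis is unaffected.

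**What to change.** Do not exclude on non-review of displayed suggestions in the sensitivity comparison. Either option will do:

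- delete criterion (4); or
- redefine it so that it does not depend on whether, or what, the AI displayed, for example the AI step not opened, logged in the same way in both arms.

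In either case, report the number of cases with unreviewed suggestions by arm and by reference-standard status.

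The cost is a wording change. The article says that choosing not to review is already recorded in the background; for the second option, check that the log also captures the AI step when nothing is displayed. The downside of deletion is that the remaining listed exclusions are those of the mITT set, so the per-protocol set would nearly coincide with it. The redefinition keeps a distinct set.

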### Eligibility and baseline assessment

For each included participant, the following baseline characteristics will be collected:Demographic information: gender, age, weight (kg), height (cm), education, nationality, registered residence (rural or urban), permanent address;Clinical information: Chief complaint, symptoms, indications, signs, baseline mRS;Medical history: History of intracranial aneurysms, history of head surgery, family history of SAH and intracranial aneurysms, comorbidities such as hypertension, diabetes mellitus, and cardiovascular disease;Lifestyle habits: Smoking, drinking, sleep pattern, exercise, occupation;Life quality evaluation: EuroQol 5-Dimensional, 5-Level (EQ-5D-5L) scores, sleep and psychosocial indexes (Shift Work Assessment, Pittsburgh Sleep Quality Index (PSQI), Patient Health Questionnaire-9 (PHQ-9), Hospital Anxiety and Depression Scale (HADS), Short-Form 36 Health Survey (SF-36);Information from the head CTA and report: Radiology report of head CTA, details on the number, location, size, and morphology of aneurysms, time taken for interpretation, PHASES score [26], and ELAPSS score [27] for unruptured and untreated aneurysms;Others: AI interpretation results, time of Workstation manipulation.

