### Outcomes

#### Primary outcomes

When the enrollment is finished, the true-positive, false-positive, true-negative, and false-negative diagnosed aneurysms will be derived from the released reports against the reference standards. The primary outcome measures are coprimary endpoints of superiority in patient-level sensitivity and noninferiority in specificity (with a noninferiority margin of 5% [31]) for the True-AI arm to the Sham-AI arm in intracranial aneurysms. The patient-level sensitivity is defined as the proportion of patients with true-positive diagnosed aneurysms among patients with positive reference standards. The specificity is defined as the proportion of patients with true-negative aneurysms among patients with negative reference standards.

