#### Secondary outcomes (Table S1)

Differences of other diagnostic performance metrics for intracranial aneurysms between True-AI and Sham-AI group, including accuracy, lesion-level sensitivity, positive predictive value (PPV), and negative predictive value (NPV).Differences of the diagnostic performances for other intracranial lesions between True-AI and Sham-AI group, including patient-level sensitivity, specificity, accuracy, PPV, and NPV for intracranial arterial stenosis (≥ 50%), occlusion, and intracranial tumors.Differences of the detection rates of intracranial lesions according to radiology reports between True-AI and Sham-AI group, including intracranial aneurysms, intracranial arterial stenosis (≥ 50%), occlusion, and intracranial tumors.Differences of the workload of head CTA interpretation between True-AI and Sham-AI group, including the time (seconds) of interpreting head CTA images and the number of consensus meetings (times).Differences in the proportion of participants with resource use between True-AI and Sham-AI group, including the number of care encounters (in person) during follow-up, the number of care encounters (in person) for aneurysms during follow-up, and the total number of cerebral artery tests (including DSA, CTA, MRA, and high-resolution vessel wall MR imaging) at the 3-month and 12-month follow-ups.Differences in the proportion of participants with treatment-related clinical events between True-AI and Sham-AI group including clinical follow-up, hospitalization (number of subsequent hospitalizations, number of hospitalization for intracranial aneurysms, in-hospital mortality rate, morbidity with modified RS ≥ 3 due to intracranial hemorrhage or treatment, length of hospital stay), patients undergoing DSA (detection rate of intracranial aneurysms among DSAs, detection rate of no abnormality among DSAs), patients with different methods for aneurysm treatment (conservative/coil/clip/others), patients with aneurysm treatment-related complications (intraoperative rupture, death, stroke, etc.), patients with recurrence or residual intracranial aneurysm after surgery at the 3-month and 12-month follow-up.Differences of life quality evaluation between True-AI and Sham-AI group including EQ-5D-5L scores, sleep and psychosocial indexes (shift work assessment, PSQI, PHQ-9, HADS, SF-36, mRS) at both the 3-month and 12-month follow-up assessments.Differences in the proportion of participants with outcomes of aneurysm-related events between True-AI and Sham-AI group including all-cause mortality, mortality of aneurysm rupture, aneurysm growth, aneurysm rupture, SAH, and stroke (hemorrhagic stroke, ischemic stroke) at the 3-month and 12-month follow-ups.Differences in the incremental cost-effectiveness ratio (ICER) between True-AI and Sham-AI group at 3-month and 12-month follow-up. We will calculate quality-adjusted life years (QALYs) by using the EQ-5D-5L life quality questionnaire at the 3-month and 12-month follow-up for the True-AI and Sham-AI arms. Healthcare costs per patient will be calculated as the sum of inpatient, outpatient, testing, and pharmaceutical costs during the follow-up period for the two arms. We will divide the difference in healthcare costs by the difference in QALYs to calculate the ICER of the True-AI arm compared to the Sham-AI arm. To determine whether the True-AI arm is cost-effective, we will use cost-effectiveness thresholds with an ICER < $38,070 per QALY gained will be considered cost-effective (Highly cost-effective was defined as an ICER less than 1 time the per capita gross domestic product (GDP) in China; cost-effective, an ICER of 1 to 3 times the per capita GDP; and not cost-effective, an ICER greater than 3 times the per capita GDP [32]. The per capita GDP in China in 2023 was US $ 12,690). We will conduct deterministic sensitivity analysis on all QALYs and cost parameters, typically by one-way or two-way sensitivity analyses. One-way sensitivity analysis involves systematically varying individual parameters through plausible values while holding all other values constant and assessing the impact of these individual variations, while two-way sensitivity analysis involves varying two parameters simultaneously. Our sensitivity analysis will address the uncertainty in the estimation of QALYs and cost parameters and assess its impact on cost-effectiveness results.

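### The only confidence interval method named, Clopper-Pearson, ignores within-patient clustering in lesion-level sensitivity and cannot give an interval for the between-arm difference (minor)

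*Protocol article*

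**What the plan says.** The Data analysis plan contains one sentence on interval estimation: "A 95% CI will be calculated using the Clopper-Pearson method". It names no parameter, makes no exception and gives no second method.

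Under Secondary outcomes, the first item is the between-arm difference in further aneurysm metrics, "including accuracy, lesion-level sensitivity, positive predictive value (PPV), and negative predictive value (NPV". The Data analysis plan also lists subgroups by "Size (< 5 mm vs. ≥ 5 mm) and locations of intracranial aneurysms", without saying whether they are counted by patient or by lesion.

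The primary outcome has one result per patient: "The patient-level sensitivity is defined as the proportion of patients with true-positive diagnosed aneurysms among patients with positive reference standards".

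The article allows for several aneurysms in one patient. Under Interventions (after Fig. 2), the junior radiologist must "input the three-dimensional coordination of each diagnosed aneurysm in the study website". The baseline data include "details on the number, location, size, and morphology of aneurysms". Under Description of the investigational product, the True-AI model "had a patient-level sensitivity, lesion-level sensitivity and specificity of 0.93, 0.87, and 0.79" in the validation dataset. The article gives neither the mean number of aneurysms per patient nor a within-patient correlation.

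**The concern.** Clopper-Pearson is exact for a count of independent binary trials. A pooled lesion count is not of that kind once some patients contribute two or three aneurysms. The same scan, junior reader, AI run and senior review decide all lesions of one patient, so positive correlation between their results is plausible. In that case the true standard error exceeds the binomial one and the interval covers less often than stated.

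The second difficulty needs no assumption about correlation. The outcome is a difference between two arms, and Clopper-Pearson describes one proportion in one sample. Two separate intervals, one per arm, are not an interval for the difference.

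At stake is the stated precision of one secondary outcome, and of the size subgroups if they are counted by lesion.

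**Working it through.** **1. The plan's own figures, to fix the denominators.** Sensitivity 0.65 versus 0.75, one-sided alpha 0.025, power 0.80:

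n per arm = [1.960·√(2·0.70·0.30) + 0.842·√(0.65·0.35 + 0.75·0.25)]² / 0.10² ≈ 329.

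Allowing for 5% attrition, 329/0.95 gives 347 per arm, or 694 in total, as stated. The final sample has 6450 × 0.12 = 774 aneurysm patients, or 387 per arm. After attrition, 387 × 0.95 ≈ 367 remain. Power then computes to 0.842 (stated 0.841). So about 367 aneurysm patients per arm is a fair base.

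**2. Do multiple aneurysms occur?** Assume the validation study defined patient-level sensitivity as the Primary outcomes section does. Then detected lesions number at least 0.93 per positive patient. Detected lesions are also 0.87 of all lesions. Hence lesions per positive patient ≥ 0.93/0.87 ≈ 1.07 (0.925/0.875 ≈ 1.06 allowing for rounding). This is a floor for the validation set. It says nothing about the correlation, and the trial population may differ.

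**3. Design effect.** DE = 1 + (E[m²]/E[m] − 1) × ICC, where m is the number of lesions in a positive patient. The lesion splits and the ICC range of 0.2 to 0.6 are assumptions, not figures from the article.

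- 1/2/3 lesions in 80/15/5% of patients: E[m] = 0.80 + 0.30 + 0.15 = 1.25 and E[m²] = 0.80 + 0.60 + 0.45 = 1.85, ratio 1.48. DE = 1 + 0.48 × ICC, or 1.10 to 1.29. Since 1 − 1/√DE runs from 0.04 to 0.12, intervals are about 4 to 12% too narrow.
- 1/2/3 lesions in 70/20/10% of patients: E[m] = 0.70 + 0.40 + 0.30 = 1.40 and E[m²] = 0.70 + 0.80 + 0.90 = 2.40, ratio 1.71. DE = 1 + 0.71 × ICC, or 1.14 to 1.43.

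**4. Coverage of the nominal 95% Clopper-Pearson interval on pooled lesions.** Beta-binomial simulation, 367 patients per arm, at least 6000 runs per scenario. The first two rows use sensitivity 0.70. The others use 0.65 and 0.75, the article's patient-level values taken as proxies.

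| Mean lesions per positive patient | ICC | Coverage |
|---|---|---|
| 1.25 (80/15/5) | 0.2 to 0.6 | about 94%, falling to 92% |
| 1.4 (70/20/10) | 0.2 to 0.6 | about 94%, falling to 90–91% |
| 1.1 | 0.3 to 0.5 | 94.7–95.1% |
| 1.1 to 1.5 | 0.1 | 94.7–95.4% |
| 1.1 to 1.5 | 0 | 95.4–96.0% |
| 1.5 | 0.8 (extreme) | 87.8% |

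**5. Effect on width.** At sensitivity 0.75 and mean 1.25, the Clopper-Pearson interval is 0.081 wide. Multiplying by √DE gives 0.081 × 1.065 ≈ 0.086 at ICC 0.3 and 0.081 × 1.107 ≈ 0.090 at ICC 0.5.

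**The case against.** The strongest reply is that the interval sentence is generic. It does not mention lesion-level sensitivity, and handling of clustering for one secondary metric is commonly left to the SAP, which is not shown. This carries weight and lowers the importance of the point. It does not remove it: the article states one method without exception, and that method does not fit an outcome the article lists.

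It can also be said that Clopper-Pearson is conservative and absorbs mild clustering. That is right. The rows with a mean of 1.1 or an ICC of 0.1 show almost no loss of coverage.

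Four stronger readings are tempting and should not be drawn:

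- *The plan prescribes Clopper-Pearson for every proportion.* It does not say so. It is only the sole method named.
- *The location results are also too narrow.* Splitting lesions over locations separates lesions of the same patient, so clusters shrink. With lesions spread evenly and independently over the seven listed sites (an assumption), simulated coverage within a site was 95.4–96.6%. With two equal size classes it was 94.0–95.4% (80/15/5 split) or 93.1–95.2% (70/20/10 split), so any effect on size subgroups is small. The article does not say that either subgroup is counted by lesion.
- *The between-arm comparison has an inflated error rate.* A naive test on pooled lesions would be inflated, to about 6–10% in these scenarios. But the chi-square or Fisher test is assigned to the two primary outcomes, and no test is prescribed for lesion-level sensitivity.
- *The trial's main conclusion is at risk from clustering.* Both coprimary endpoints have one result per patient, so it is not. The lack of a named two-sample interval also matters for the 5% specificity margin, but that is a separate question from clustering.

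**Conclusion.** The point holds as a minor one, in two parts.

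First, the sole named interval method ignores within-patient dependence when applied to pooled lesion-level sensitivity. The interval is then too narrow, on condition that some patients have several aneurysms and that their results are positively correlated. The article supports the first condition. The second is plausible but not documented. Under the assumed mid-range inputs the loss is roughly one to five percentage points of coverage, and it is close to nil when multiple aneurysms are few or correlation is low.

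Second, and without any such condition, a one-sample interval cannot describe the between-arm difference by which the outcome is defined.

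**What to change.** Replace the single interval sentence with three short statements:

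- Clopper-Pearson is used for single-arm, patient-level proportions.
- Pooled lesion-level sensitivity, and the size subgroups if counted by lesion, get an interval that takes the patient as the cluster: a bootstrap resampling patients, or GEE/robust variance.
- The True-AI minus Sham-AI difference is reported with a two-sample interval, clustered by patient for lesion-level outcomes.

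The size subgroups should also be declared as counted by patient or by lesion. No new data are needed, since each aneurysm and the number per patient are already recorded. The cost is slightly wider intervals (in the example above, 0.086 to 0.090 instead of 0.081) and a little more analysis work.
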